## Results

This study is designed to fill a gap in Canadian evidence on the impact of hypoglycemia on HEOR outcomes. More specifically, it will generate productivity and utility inputs for economic modeling of T2DM. Insulin therapy is expensive, and hypoglycemia is a significant component of economic evaluation. Robust HEOR data may help HTA agencies in future reimbursement decision-making.

## Discussion

### Strengths and Limitations

Insulin-induced hypoglycemia is a burden to patients with diabetes, and this study will collect HEOR estimates reflecting how SHEs and NSHEs negatively affect patients’ productivity and utility. To our knowledge, this would be the first Canadian real-world study to attempt to longitudinally measure the impact of hypoglycemia on utility and productivity loss, including absenteeism, presenteeism, and unpaid work, in insulin-treated patients with T2DM. In this study, hypoglycemia will be categorized into SHEs and NSHEs without further subgrouping by severity (eg, mild or moderate) or time of occurrence (daytime or nocturnal). This classification is preconized by HTA agencies for CUAs in T2DM [6,7]. Subjective measurement of hypoglycemia may overestimate the number of episodes, which may underestimate the outcome values by event (conservative approach). In addition, the recently published guidelines by the International Hypoglycaemia Study Group recommend that the hypoglycemia threshold be lowered to <3.0 mmol/L (<54 mg/dL) in clinical trials [54]. This threshold was suggested because it is sufficiently low to indicate serious, clinically important hypoglycemia and because this level does not occur under physiological conditions in individuals who do not have diabetes. A joint position statement by the ADA and the European Association for the Study of Diabetes was subsequently published, which indicated that the glucose level should be lowered for clinical trials [54]. The use of the official definition of hypoglycemia (≤3.9 mmol/L) instead of a lower threshold might lead to overreporting of nonclinically serious events. Nevertheless, this approach is also conservative as it underestimates the outcome values by event. Defining hypoglycemia based on symptoms or blood glucose measurements is considered a reliable method that best reflects real-world practice [18,19]. The frequency of assessments (recall period) was based on previous Canadian studies [18,19]. The use of diary records (if higher than the number reported in the questionnaire) can compensate for potential recall bias and is a conservative approach as it would decrease the outcome values by event. Considering that longitudinal studies usually have a minimum of 3 measurements and that the frequency of assessments is 4 weeks, the duration of the study is therefore 3 months.

The outcomes will be measured using validated questionnaires. Although several instruments are available to estimate productivity losses, there is no gold standard [55]. In addition, HTA agencies make different recommendations regarding types of productivity losses (absenteeism, presenteeism, and unpaid work) to include in economic evaluations and methods for valuation or monetization (human capital approach and friction approach) [33]. Therefore, productivity losses will be presented as total and type-specific raw scores (number of hours per day) and will not be transposed into monetary value. This approach provides flexibility and allows future economic evaluations to be fit for specific purposes. The *i*PCQ scoring manual presents different valuation methods depending on various scenarios (eg, presence of long-term absences and frequency of measurements) and is fully adaptable to different HTA requirements [33]. It is recommended that the choice of a work productivity instrument for economic evaluations should be based on purpose, perspective, practicality, population, and psychometrics (5 *P*s) [55]. The *i*PCQ meets the 5 *P*s criteria as it is a validated generic instrument that allows monetization, captures all types of productivity losses, and minimizes the burden to patients (has short completion time and is easy to understand). Owing to its recent development, the use of the *i*PCQ is less extended than older questionnaires, which comes with the advantage that questions are optimized based on 3 previously validated instruments [33]. Moreover, this promising instrument has a recall period of 4 weeks, which matches measurements of hypoglycemia while limiting recall bias. Although there is no gold standard, the Work Productivity and Activity Impairment Questionnaire is the most widely used instrument to assess productivity losses [56]. Similar to the *i*PCQ, the Work Productivity and Activity Impairment Questionnaire covers absenteeism, presenteeism, and unpaid work, but over a shorter period. As the recall period is only 7 days, it may not capture all productivity losses due to hypoglycemia if events occur outside of the recall period. Regarding utility, the use of generic preference-based instruments is recommended, among which the EQ-5D is the most extensively used [57]. The EQ-5D asks patients how they feel on that day without any recall period. Therefore, for complications associated with transient effects only (eg, diarrhea), utility should be measured simultaneously (ie, on the same day). When acute events are followed by persistent fear and anxiety (eg, stroke), different measurement timings can be used. If the utility is measured shortly after the event, the punctual effect of the complication will be captured. If utility is not measured concurrently, then a general effect will be captured. For economic modeling of T2DM, utility values recommended by HTA agencies were all sourced from studies designed to capture the general impact of diabetic complications, including hypoglycemia [6,7]. In a reference study by Currie et al [5], the EQ-5D captured decrements in utility due to hypoglycemic events that occurred over the last 3 months. Furthermore, in several randomized controlled trials, the impact of SHEs on utility was measured for up to 1 year after the event [36,58,59]. A limitation of this approach is the underestimation of acute physical effects related to the event. Indeed, the current design may capture the psychological effects of hypoglycemia more accurately. Nevertheless, this study will estimate the overall impact of this treatment-related adverse effect on utility, providing relevant inputs for T2DM economic modeling.

Confounding is a concern in observational research [28]. Before implementing this study, independent variables were thoroughly identified, and each known variable will be measured to limit confounding. To reflect real-world practice, independent variables that will be extracted from patients’ medical files will represent the last available value, which may not reflect the current unknown value. Moreover, some independent variables will be self-reported, potentially leading to residual confounding. Nevertheless, there are no unmeasured known confounders, and the potential impact of an unmeasured unknown confounder will be tested using *E* values [52,53]. There is evidence that a cross-sectional design may overestimate the impact of T2DM complications on utility because of the underlying heterogeneity across patients [37]. Therefore, a longitudinal design with time-varying exposure will help protect against time-invariant confounding (natural heterogeneity) [40,46-48]. A GEE model will be used to account for the correlation associated with repeated measures from the same individual. Although mixed models provide a flexible framework compared with the GEE model, they require a large sample size and may be computationally demanding. Therefore, the simpler GEE method will be used to deal with this noncomplex data set (no large-scale data analysis, single level of clustering, and absence of nonstochastic time-varying covariates, eg, time from baseline). In addition, it is acknowledged that a GEE model is comparable with a random intercept model for continuous outcomes. A drawback of the GEE model is the assumption that the data are MCAR [40,46-48]. Therefore, if the data are not MCAR, the WGEE will be used to ensure the robustness of the estimates [50]. Furthermore, reminders and incentives should help to minimize the rate of missing data.

Patients will be recruited from several regions throughout Quebec and Ontario, Canada, to increase the external validity of the results. However, recruitment sites will be limited to urban areas and may not be representative of rural areas. The real-world design and broad eligibility criteria will ensure that the HEOR estimates are generalizable to a target population for future reimbursement purposes. It is assumed that recruitment through clinical sites only will not affect the representativeness of the sample as patients with diabetes have regular follow-ups with their health care providers, thereby capturing most eligible patients and not only patients in worse condition. Furthermore, enrolling patients from both medical and diabetes clinics will be representative of the target population. Although probability sampling is the gold standard for ensuring sample representativeness, it is often not feasible in Canada because many jurisdictions lack electronic patient databases, particularly family practice. Yet, systematic participant recruitment as consecutive sampling using appointment lists also helps minimize selection bias (including oversampling). Participation rates will be recorded to document the risk of selection bias. It should be noted that the COVID-19 pandemic may affect patient productivity and utility. However, given the use of the GEE model to estimate the independent impact of hypoglycemia on the HEOR estimates, the results are expected to be valid and generalizable.

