**Methods:**

This noninterventional, multicenter, 3-month prospective study will recruit patients from 4 medical clinics and 2 endocrinology or diabetes clinics. Patients will be identified using appointment lists and enrolled through consecutive sampling during routinely scheduled consultations. To be eligible, patients must be aged ≥18 years, diagnosed with T2DM, and treated with insulin. Utility and productivity will be measured using the EQ-5D-5L questionnaire and Institute for Medical Technology Assessment Productivity Cost Questionnaire, respectively. Questionnaires will be completed 4, 8, and 12 weeks after recruitment. Generalized estimating equation models will be used to investigate productivity losses and utility decrements associated with incident hypoglycemic events while controlling for individual patient characteristics. A total of 500 patients will be enrolled to ensure the precision of HEOR estimates.

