### Study Procedures

#### Data Collection

The sociodemographic and clinical characteristics of the patients will be collected at recruitment. Patients will complete a baseline questionnaire to report their age, gender, ethnicity, education, income level, employment status, living status, alcohol consumption, smoking, and physical activity. As a proxy for frailty, the self-reported number of visits to a health care provider over the last 3 months and the number of emergency visits and hospitalizations over the last 6 months will also be collected [28]. As a proxy for lifestyle habits, immunization status (pneumococcal, influenza, and COVID-19) will also be self-reported. Self-care (disease management activities) will be assessed using the Diabetes Self-Management Questionnaire, a validated questionnaire covering behaviors related to glycemic control (diet, blood glucose monitoring, medication adherence, physical activity, and contact with health care professionals) [29]. The type of device used for glucose monitoring will also be recorded (eg, traditional finger-prick monitor and flash glucose monitoring device). It should be noted that continuous glucose monitoring systems are not reimbursed in T2DM, thereby limiting their use. To describe the history of hypoglycemia, patients will also be asked if they have experienced NSHEs and SHEs over the last 3 months and the last year, respectively. The duration of diabetes, glycated hemoglobin (HbA_1c_), BMI, therapy, duration of insulin, and vascular complications will be extracted from the patients’ medical records.

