#### Assessments and Study Calendar

Patients will complete a self-assessment questionnaire (SAQ) at 4, 8, and 12 weeks to report the number of NSHEs and SHEs experienced in the last 28 days. Patients will also be provided with a diary to prospectively record hypoglycemic events. Both the SAQ and the diary will be used to estimate the number of hypoglycemic events. The EQ-5D and *i*PCQ will also be completed at 4, 8, and 12 weeks. The study calendar is shown in Figure 1. The questionnaires will be completed electronically via a web-based platform. To ensure that patients complete their questionnaires in a timely manner, reminders will be sent to them via email. Paper-based questionnaires can be provided to participants who do not have access to or are less familiar with using the internet (phone call reminders).

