#### Independent Impact of Hypoglycemia

Generalized estimating equation (GEE) models will be used to investigate productivity losses and utility decrements associated with incident hypoglycemic events while controlling for individual patient characteristics. For utility, two separate models will be presented: one for the EQ-5D index and one for the visual analogue scale. For productivity losses, one main analysis will be presented for the total number, and separate models for each module will be presented as a complementary analysis. The potential model-confounding covariates are presented in Table S1 in Multimedia Appendix 1. Independent variables were identified based on existing literature and previous work from the Alliance for Canadian Health Outcomes Research in Diabetes [34]. Diabetes complications (micro- and macrovascular) to be included in the models are those preconized by HTA agencies for CUAs in T2DM [4,6,7]. On the basis of the current reference study for hypoglycemic utility values [5], the number of hypoglycemic episodes will be log-transformed to facilitate model fitting. The original scale will be tested using sensitivity analyses. Moreover, transformations of continuous independent variables will also be tested in the sensitivity analyses (Table S1 in Multimedia Appendix 1). The presence of multicollinearity will be tested, where important collinearity will be defined as a variance inflation factor of >10. Owing to the short duration of the study, all covariates, except hypoglycemia, will be considered time invariant for model simplicity. If vascular complications occur during the study period (incident cases), a history of macrovascular and microvascular complications will be treated as a time-varying covariate. The main models will not include interaction terms, as large-scale studies evaluating the impact of diabetes complications on utility have not demonstrated any interaction between vascular events and event history and among the different vascular events [35-37]. A sensitivity analysis will be performed to test for the interaction between hypoglycemic events and determinants, namely, a history of hypoglycemia and diabetes complications.

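### The planned GEE gives only partial protection against time-invariant confounding, because its coefficient blends between-patient and within-patient slopes and no outcome is recorded at recruitment

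*Protocol article*

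**What the plan says.** In Strengths and Limitations, the protocol article notes that cross-sectional studies may overstate the effect of complications on utility because patients differ from one another. It then concludes that "a longitudinal design with time-varying exposure will help protect against time-invariant confounding (natural heterogeneity". The analysis that has to deliver this is set out under Independent Impact of Hypoglycemia:

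- "Generalized estimating equation (GEE) models will be used to investigate productivity losses and utility decrements associated with incident hypoglycemic events", adjusted for patient characteristics.
- The exposure enters as one term: "the number of hypoglycemic episodes will be log-transformed to facilitate model fitting". The original scale is a sensitivity analysis.
- "all covariates, except hypoglycemia, will be considered time invariant for model simplicity", apart from vascular complication history if incident cases occur.
- The working correlation is chosen by QIC, with exchangeable as the choice if results are similar.

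No patient fixed effects, within/between split or change score is described.

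On timing, the abstract states: "Questionnaires will be completed 4, 8, and 12 weeks after recruitment". Assessments and Study Calendar says the same of the EQ-5D and iPCQ, which "will also be completed at 4, 8, and 12 weeks". Data Collection says: "The sociodemographic and clinical characteristics of the patients will be collected at recruitment". Its list includes hypoglycemia history, self-care and frailty proxies, but neither outcome questionnaire.

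**The concern.** Repeated measures remove stable patient differences only to the extent that the coefficient is identified from change within patients. A marginal GEE with a single exposure term also uses the contrast between patients with frequent and rare hypoglycemia, which is the contrast a cross-sectional study uses. If patients in worse stable health also have more events, for reasons the covariates do not capture, the decrement comes out too large. That is the same direction of error the article says its design guards against.

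Strengths and Limitations calls the GEE comparable with a random intercept model. That model likewise assumes patient effects unrelated to exposure, so the comparison does not rescue the claim. The E values planned under Unmeasured Confounding describe robustness but remove no bias.

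The decrement matters because Study Rationale and Relevance reports that incremental cost-effectiveness ratios were very sensitive to it. The study's purpose is to supply the decrement together with usable SEs and CIs.

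**Working it through.** **Sample size used.** The article's figures reproduce: 68/0.17 = 400 evaluable, and 400/(1 - 0.20) = 500 enrolled. The check uses 400 patients with 3 visits.

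**Weight on the between-patient slope.** For a linear GEE with exchangeable correlation ρ, m = 3 visits and exposure intraclass correlation ICCx:

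coefficient = w × between slope + (1 - w) × within slope, where w = kB/(kB + W), k = (1 - ρ)/(1 + 2ρ), B = 1 + 2·ICCx, W = 2(1 - ICCx).

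The article gives neither correlation, so w is shown over a range:

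| ICCx | ρ = 0 | ρ = 0.5 | ρ = 0.7 | ρ = 0.85 |
|---|---|---|---|---|
| 0.2 | 0.47 | 0.18 | 0.10 | 0.05 |
| 0.6 | 0.73 | 0.41 | 0.26 | 0.13 |
| 0.8 | 0.87 | 0.62 | 0.45 | 0.27 |

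For example, at ICCx 0.6 and ρ 0.7: k = 0.3/2.4 = 0.125, B = 2.2, W = 0.8, and w = 0.275/1.075 = 0.26. The weight shrinks as ρ rises but is never zero.

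**Size of the bias, event scale.** All inputs are assumptions: utility SD 0.20, utility ICC 0.7, mean 1.5 nonsevere events per 28 days, lognormal event propensity with SD 1, true decrement 0.0060, and residual correlation r between stable utility and log propensity.

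- Variance of the patient rate: 1.5² × (e - 1) = 3.87. Poisson variance: 1.5. ICCx = 3.87/5.37 = 0.72.
- With ρ = 0.7: k = 0.125, B = 2.44, W = 0.56, w = 0.305/0.864 = 0.353.
- SD of stable utility: 0.20 × √0.7 = 0.167. At r = -0.2, the between-slope bias is 0.2 × 0.167 × 1.5/(3.87 + 1.5/3) = 0.0502/4.37 = 0.0115.
- Expected GEE decrement: 0.0060 + 0.353 × 0.0115 = 0.0101. At r = -0.1 it is 0.0080.

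**Simulation with the same inputs** (true value 0.0060 per event, or per unit of log count):

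| r | Exchangeable GEE, per event | Coverage | Exchangeable GEE, per log unit | Coverage |
|---|---|---|---|---|
| -0.1 | about 0.008 | about 87% | about 0.012 | about 88% |
| -0.2 | 0.0101 | 64% | about 0.018 | about 66% |

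At r = 0 there is no bias. With the count split into patient mean and visit deviation, the within-patient coefficient on the event scale stays at 0.0060 to 0.0063. Its SE is 0.0031 against 0.0025 (0.0031/0.0025 = 1.24).

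**How much the design does remove.** At r = -0.2 on the event scale, an independence fit, which stands in for a cross-sectional analysis, gives 0.0158. The bias falls from 0.0098 to 0.0041, and 0.0057/0.0098 = 58% is removed.

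**Second simulation, different confounder set-up** (120 replicates per setting, true effect 0.005 per log unit). An unmeasured stable confounder lowered utility by 0.02, 0.05 or 0.10 per SD:

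- The exchangeable GEE gave decrements of 0.0097, 0.0171 and 0.0236, with coverage 84%, 41% and 8%.
- The independence fit gave 0.0186, 0.0419 and 0.0787.
- The within-patient coefficient stayed at 0.0050 to 0.0055, with coverage 92% to 97%, with or without the confounder.

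**The case against.** The strongest reply is that the sentence claims only help, and help is what the model gives: under the inputs above, more than half of the cross-sectional bias goes. This stands. A reader might infer that the protection is absent, or that the decrement carries the full cross-sectional overestimate. The article's own model does not support either reading.

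The bias also depends on a residual correlation that the article does not give. The plan adjusts for measured covariates, and Data Collection gathers hypoglycemia history, HbA1c, complications, self-care and frailty proxies. It also admits possible residual confounding, since chart values may be out of date and some covariates are self-reported. So the bias is conditional, though it is not implausible.

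A reader might next infer that the within-patient coefficient should simply replace the planned one. Definition of Hypoglycemia argues against that: the study is meant to capture the overall effect, including lasting fear, and fear in frequent sufferers lies largely in the between-patient slope. In an assumed setting with a causal fear effect of 0.010 per unit of long-run event rate and no confounding, the overall effect was 0.016. The planned GEE gave 0.0089 and the within-patient estimate 0.0060, which is further from the target.

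For severe events the bias may be smaller. In one assumed setting (about 82 of 400 patients with an event, correlation -0.2) the GEE gave 0.053 against a true 0.047, about +13% or roughly half an SE.

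**Conclusion.** The point holds in a limited form. The design and model together protect in part against time-invariant confounding. How far depends on the working correlation, on how stable each patient's event rate is, and on the measured covariates. Unmeasured stable confounding stays partly in the decrement. The overestimate for nonsevere events is about one third to two thirds on the event scale (0.008/0.006 and 0.0101/0.0060) at residual correlations of -0.1 and -0.2, and larger on the log scale that the main model uses. It is nil at zero correlation. None of the correlations or confounder strengths comes from the article.

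The article asserts the protection without a model that would show how much of the estimate comes from each source, and without saying whether the intended decrement is the within-patient or the overall effect. Table S1 and Figure 1 are not shown, but the text is explicit on when the questionnaires are given.

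**What to change.** 1. Prespecify, beside the main GEE, a model that splits the log event count into the patient's mean over follow-up and the visit-specific deviation from it. Report both coefficients with SEs and CIs. Do not make the within-patient coefficient the sole primary result.
2. State which effect is the intended decrement: within-patient, or overall including persistent fear as described under Definition of Hypoglycemia.
3. Add the EQ-5D-5L and iPCQ to the questionnaire already completed at recruitment. Describe them as a baseline record, not a pre-exposure value, because patients already use insulin and may have had hypoglycemia. This cannot be recovered after enrolment.
4. Reword the sentence in Strengths and Limitations as partial protection that depends on the working correlation and the measured covariates.

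Cost: one derived variable, a few sentences, and a few more minutes per patient at recruitment. The within-patient SE is about 15% to 25% larger, and within-patient estimates for severe events will be imprecise, with about 68 patients expected to have one.

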## Methods

### Research Purpose and Study Design

This noninterventional, multicenter, 3-month prospective study is designed to collect HEOR inputs for future economic modeling. This study will generate descriptive HEOR estimates that can be incorporated into T2DM models, along with precision parameters (ie, CIs and SEs) to evaluate uncertainty in CUAs in sensitivity analyses. Considering the nature of the disease, a longitudinal design with repeated measures was deemed appropriate to limit confounding and increase the quality of evidence.

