Distributions of outcomes will be examined considering the expected nature of productivity data (right-skewed and excess zeros) and utility data (left-skewed, censored, and ceiling effect). Although utility is commonly left-skewed, the distribution of utility scores may vary greatly between health conditions depending on the severity. Left skewness is more common when the studied condition is associated with mild symptoms, whereas severe health states may even lead to negative values representing conditions worse than death [38]. One major advantage of the GEE is the avoidance of distributional assumptions, where several distributions can be tested. Several large-scale longitudinal studies evaluating the impact of diabetes complications on utility, including the landmark United Kingdom Prospective Diabetes Study, used models fitted under a linear framework [35-37]. Common alternatives to the Gaussian distribution with identity link function include the Gaussian distribution with log link, negative binomial distribution with log link, gamma distribution with identity link, and gamma distribution with log link. The gamma distribution requires nonzero positive continuous data; thus, utility must be transposed into disutility (1−utility value). A beta binomial distribution can also be used with a transformation (linear transformation or rescaling) to fit the restrictive open interval (0,1), which excludes the end points 0 and 1 [39]. For the use of health care resources, nonlinear options mostly include negative binomial distribution (for resource use) and gamma and inverse-Gaussian distribution with log link function (for costs). Raw outcome data will be explored, where distributions will be depicted using histograms and normal probability plots. The selection of the model will be based on predictive performance and goodness of fit, with the lowest values for the root mean square error and the mean absolute error and the highest values for pseudo-*R*^2^. Moreover, the model performance will also be calculated using the quasi-likelihood under the independence model criterion (QIC), where the lowest values are the best. QIC and QIC*u* will be used for correlation structure selection and variable selection, respectively. As no distributional assumptions about the response variable are made, the regression parameters cannot be estimated using the maximum likelihood method. Thus, quasi-likelihood statistics will be used (pseudo-*R*^2^, QIC, and QIC*u*) instead of the well-known likelihood statistics (*R*^2^, Akaike information criterion, and Bayesian information criterion) [40]. Different variance-covariance structures are available to fit the relationship between responses. In health economics, common choices include exchangeable correlation structure (observations from the same cluster are equally correlated), autoregressive (correlation decreases with time), and unstructured (different and complex correlations). According to the Good Research Practices for Retrospective Database Analysis Task Force recommendations by the International Society for Pharmacoeconomics and Outcomes Research, if results are similar with different matrices, an exchangeable matrix will be used [41]. Regression diagnostics will be performed to explore the presence of influential observations and outliers (Cook distance and residual plots). Exclusion of extreme values will be tested in sensitivity analysis. All results will be expressed as coefficients, SEs, 95% CIs, and associated *P* values (2-sided tests at the .05 significance level). Full regression models and adjusted effects will be presented. All statistical analyses will be performed using R (R Foundation for Statistical Computing) [42].

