
#### Sample Size

As per good research practices, the sample sizes for utility estimates should be based on precision rather than hypothesis testing [38,43]. Indeed, there is no consensus on the use of minimally important differences in EQ-5D measures for statistical power calculations [31,44]. Therefore, the sample size was determined to ensure reasonable variability around the utility value for SHEs (which also ensures precision for NSHEs as the incidence is significantly higher). However, no value for the expected SD was found in the literature for performing a reliable precision-based sample size calculation. A literature review was performed to identify studies that estimated utility values for hypoglycemia. However, it is often difficult to find an expected SD for utility values because they are sensitive to the type of instrument, country, precise definition of outcome, or timeframe. Furthermore, most studies did not provide uncertainty values around the estimates. As discussed by Beaudet et al [4], utility values for hypoglycemia are limited and CIs are scarce.

Therefore, the required sample size was determined based on the study by Currie et al [5], which is used as a reference for hypoglycemic utility values by CADTH and NICE [6,7]. Currie et al [5] obtained utility estimates from 68 patients who experienced at least one SHE over a 3-month period. According to Canadian real-world studies, the 3-month incidence of SHEs among insulin-treated patients with T2DM was approximately 17% [18,19,45]. With a 3-month incidence rate of 17%, 400 patients will have to be recruited to ensure that 68 patients experience at least one SHE during the study follow-up. To account for attrition, the sample size will be increased by 20% for a target number of 500 enrolled patients. It is assumed that this sample size will also ensure the precision of the productivity estimates.

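### The sample-size reason for preferring GEE does not hold, and ordinary robust 95% CIs for the severe-event productivity coefficient would probably be too narrow with about 68 informative patients

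*Protocol article*

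**What the plan says.** Strengths and Limitations compares the two methods: "Although mixed models provide a flexible framework compared with the GEE model, they require a large sample size and may be computationally demanding". It continues: "Therefore, the simpler GEE method will be used to deal with this noncomplex data set". The other reasons given are a single level of clustering and a simple data structure. The same paragraph adds that GEE is comparable with a random-intercept model when the outcome is continuous.

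Sample Size plans on patients with at least one SHE: "400 patients will have to be recruited to ensure that 68 patients experience at least one SHE during the study follow-up". It then allows for attrition: "the sample size will be increased by 20% for a target number of 500 enrolled patients". For productivity no calculation is given: "It is assumed that this sample size will also ensure the precision of the productivity estimates".

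Independent Impact of Hypoglycemia expects productivity data to be skewed to the right with many zeros, makes the total over all modules the main productivity analysis, and log-transforms the event count. It promises: "All results will be expressed as coefficients, SEs, 95% CIs", with two-sided P values at .05. Research Purpose and Study Design explains what these are for: estimates are to be delivered "along with precision parameters (ie, CIs and SEs) to evaluate uncertainty in CUAs in sensitivity analyses".

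**The concern.** The study sets out to deliver SEs and CIs as inputs to cost-utility models. If they are too small, the uncertainty passed to those models is too small as well, and the P values are too small.

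A random-intercept model for 500 patients with three visits each is a routine fit, so sample size and computing load are weak reasons to avoid it. The robust SE normally paired with GEE is itself a large-sample tool, and what counts is how many patients carry information on the coefficient. For the SHE coefficient that is mainly the patients who have an SHE, not all 400-500. With a skewed, zero-heavy outcome, a few of those patients can dominate both the estimate and its SE. An analyst who sees 400-500 clusters would normally keep the default robust SE, and the article's reasoning gives no cue to do otherwise.

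**Working it through.** **1. The plan's own figures.** 0.17 × 400 = 68 patients with an SHE, and 400 / (1 − 0.20) = 500 enrolled. Both reproduce. Even with no attrition, 0.17 × 500 = 85.

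**2. Paid-work modules.** The article gives no employment share for this study. Assumed shares of 35% and 50% give 0.35 × 68 = 24 and 0.50 × 68 = 34 SHE patients in work. One survey cited in Current State of Knowledge had 87 workers among 150 patients (58%), which gives 0.58 × 68 = 39. These smaller numbers apply to the paid-work models only. The main total includes unpaid work, so about 68 applies there.

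**3. Simulation of coverage.** From the article: three visits, log count of events, 68 SHE patients of 400, GEE with exchangeable correlation. Assumed: zero-inflated lognormal hours (50% zeros with log-SD 0.8, or 80% zeros with log-SD 1.0), 15 baseline covariates, one or a few SHEs per affected patient, and an SHE effect of 0 or 0.7 that multiplies the outcome, so variance rises with it. Two intervals are compared:
- ordinary: estimate ± 1.96 × sandwich SE;
- corrected: estimate ± t(0.975, K − 1) × Mancl-DeRouen SE, with K the number of SHE patients.

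Results with 68 SHE patients (1,500 runs for identity link, 1,000 for log link; Monte Carlo error about 1 point):

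| Link | Zeros / log-SD | Effect | Mean SE / true SD | Ordinary | Corrected |
|---|---|---|---|---|---|
| identity | 50% / 0.8 | 0 | 0.95 | 93.1% | 94.5% |
| identity | 50% / 0.8 | 0.7 | 0.92 | 90.9% | 92.3% |
| identity | 80% / 1.0 | 0 | 0.90 | 90.6% | 91.8% |
| identity | 80% / 1.0 | 0.7 | 0.88 | 86.8% | 87.5% |
| log | 50% / 0.8 | 0 | 0.97 | 94.1% | 95.3% |
| log | 50% / 0.8 | 0.7 | 0.88 | 90.9% | 93.6% |
| log | 80% / 1.0 | 0 | 0.84 | 89.6% | 91.2% |
| log | 80% / 1.0 | 0.7 | 0.82 | 88.6% | 92.1% |

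A separate set of 1,000 runs of the fourth row gave 84.9% ordinary and 86.1% corrected, so the range at 68 is about 85-94%. An SE ratio of 0.82 means a variance of 0.82² = 0.67 of its true value.

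**4. Fewer SHE patients, same scenarios.** Ordinary coverage was 82-92% with 34 of 200 and 79-91% with 24 of 140. Corrected coverage was 84-95% and 83-95%.

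**5. Utility.** For a near-normal outcome with a ceiling, ordinary coverage was 94.2% with 68 SHE patients. A second simulation, with assumed negative binomial counts (mean 2 among those affected), gave 93-94% for EQ-5D on the log count and 90-93% on the original count.

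**6. A model-based alternative.** A constant-variance model-based interval, a rough stand-in for a random-intercept model, was run on the four identity-link rows with 68 SHE patients. It covered 94.6% and 95.1% with no effect, but 79.9% and 82.1% when variance rose with SHE.

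**The case against.** The strongest reply is that the article names no SE estimator. It could be robust, bias-corrected, model-based or bootstrapped, and the choice may sit in an analysis plan that is not shown. A reader might infer that the planned intervals are too narrow as they stand. The article does not support that; the statement is conditional on ordinary robust SEs. What remains is that the stated rationale points away from the issue.

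A reader might also take 24-34 as the number of SHE patients behind the productivity results. That range rests on an assumed employment share and concerns only complementary models. The lowest coverage figures belong there, not to the main total.

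A reader might conclude that the rationale is exactly reversed and that a mixed model would be safer. The model-based results in step 6 do not bear this out.

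Finally, few SHE patients are not the whole cause. With the same 68, utility coverage is close to nominal, so skew and zeros drive much of the shortfall. For the same reason a small-sample correction cannot be expected to cure it: with 67 degrees of freedom the t quantile is 2.00 against 1.96, only 2% wider. The article's plans to compare distributions and links, inspect Cook distances and test exclusion of extreme values address leverage, but they do not correct the SEs.

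**Conclusion.** The point holds in a limited form. Sample size is not a sound reason to prefer GEE here, although the other reasons (simplicity, one level of clustering) can stand. If ordinary robust SEs with a normal quantile are used, the SHE coefficient for total productivity would have roughly 85-94% coverage in place of 95%, a shortfall of about 1-10 points. Coverage would be lower in the paid-work models, by an amount that depends on an employment share the article does not give. EQ-5D on the planned log count, the outcome on which the study is sized, is barely touched; original-scale analyses are somewhat more exposed.

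The size rests on assumed proportions of zeros, spread, effect and SHE counts. The direction was the same in every productivity scenario run.

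**What to change.** 1. In Strengths and Limitations, delete the sample-size and computing argument against mixed models and keep the remaining reasons for GEE.
2. For SHE productivity coefficients, and for original-scale analyses, state that bias-corrected robust SEs (for example Mancl-DeRouen) will be reported with a t reference whose degrees of freedom are tied to the number of patients with an SHE.
3. Check these intervals against a bootstrap that resamples patients. The correction alone added roughly 1-3.5 points with 68 SHE patients in the table above and does not reliably reach 95%.
4. Print the number of patients with an SHE beside each SHE coefficient, separately for each module.

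The cost is a few sentences, a few lines of R and some bootstrap computing time. The intervals become somewhat wider. No new data, larger sample or change of model is needed.
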